#### Treatment As Usual

All participants were receiving usual care for HIV, which comprised pharmacological management by a physician in an infectious disease clinic setting. Generally, participants were scheduled for monthly visits with their physician and quarterly assessment of viral load and CD4 counts.

### Clinician Involvement

Apart from the single face-to-face CBT session, TXT-CBT participants may have had contact with the CBT clinician in one of two contexts. In the text CALL function, participants were prompted to text the word CALL if they needed more instruction about how to implement a particular coping skill that they had planned to use to facilitate ART adherence. When a text CALL was received, a clinician called the participant back and provided counseling to assist with the specific skill for which guidance was needed. In the text LIFELINE function, participants could text the word LIFELINE if they needed to speak to a clinician during business hours. All participants were able to use this function a total of three times during the 12-week intervention. For both text CALL and text LIFELINE functions, prior to receiving a call back from a clinician, participants received an automated response to remind them of the hours during which the clinician is available and were instructed to call 911 or go to an emergency room for any urgent matters beyond these hours or that required an immediate response. If the text was received during business hours, the clinician called the participant on the same day. For any participant who used the LIFELINE function three times or more, the protocol specified that a licensed clinician on the research team was to be consulted to determine whether a treatment referral was indicated and/or whether the participant could continue to participate in the study.

### Technical Support

Participants received weekly calls from the research staff to collect qualitative data concerning the perceived helpfulness of the TXT-CBT intervention and address any technical difficulties they may have been experiencing. A research assistant reviewed the text messaging logs regularly to monitor whether text messages were being sent on time and whether participants were engaging in texting. If participants wished to disenroll from the study they could text the keyword STOP.

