### Randomization

Following the prescreening, baseline assessment phase, and confirmation of study eligibility, participants were randomly assigned to group 1, a treatment-as-usual (TAU) condition in which participants received usual care (ie, medical management) for HIV plus a Substance Abuse and Mental Health Services Administration informational pamphlet concerning HIV and substance use (see Multimedia Appendix 1 for the pamphlet content), or group 2, a TAU plus a CBT text messaging condition (TAU+TXT-CBT). Those who were assigned to the TXT-CBT received $20 gift cards monthly over the 3-month intervention phase to offset the costs of an unlimited text messaging plan. Randomization was conducted by a research assistant using a Web-based, automated program implemented by the University of California, Los Angeles, Integrated Substance Abuse Programs Data Management Center. Neither the research staff nor participants were blinded.

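### STOP and the LIFELINE review are tied to staying in the study, not only to the messages, which opens a TXT-CBT-only route to possibly outcome-related loss of week-12 and week-24 data

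*Protocol article*

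**What the plan says.** Technical Support, on the text system: "If participants wished to disenroll from the study they could text the keyword STOP". No separate option to stop the texts and stay in follow-up is described.

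Clinician Involvement introduces the clinician functions as belonging to one arm: "TXT-CBT participants may have had contact with the CBT clinician in one of two contexts". One of them is LIFELINE: "participants could text the word LIFELINE if they needed to speak to a clinician during business hours". The allowance is stated as "All participants were able to use this function a total of three times during the 12-week intervention". The review rule begins "For any participant who used the LIFELINE function three times or more, the protocol specified that a licensed clinician on the research team was to", and goes on to require a consultation. The subject of that consultation is "whether a treatment referral was indicated and/or whether the participant could continue to participate in the study".

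The comparison arm receives usual HIV care and an "informational pamphlet concerning HIV and substance use" (Randomization). It has no text system, so neither keyword exists there.

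Statistical Analyses plans a random effects regression over the repeated observations and allows up to 20% attrition, without dividing it by arm or reason. Limitations acknowledges unequal attention and unequal data collection between the arms, but not these two routes.

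**The concern.** Ending an intervention and ending outcome follow-up are different events. When one action can do both, the trial may lose outcomes from the people whose outcomes matter most to the comparison.

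Here both actions come after randomisation and are available in one arm only. A participant who texts STOP may be disengaging. A participant who uses LIFELINE three times has repeatedly needed to speak to a clinician. A link with relapse or poor adherence is plausible in either case, though the article does not show one. If such participants leave follow-up, the remaining TXT-CBT group could look better than the group that was randomised.

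Aim 3 is exposed in a second way. It plans to relate change in self-efficacy to treatment retention and to substance use during and after treatment, which needs outcomes from people who stop treatment. If stopping the texts also means leaving the study, treatment retention and study retention cannot be told apart, and change scores are missing for those with low retention.

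**Working it through.** **Inputs from the protocol article**
- Sample Size: 25 per group.
- Statistical Analyses: detectable d about 0.7; correlation over time 0.50; attrition up to 20%; power 0.80; one-sided alpha 0.05; SD about 27 points; detectable differential change about 19 points.
- Study Design and Table 1: visits at baseline and weeks 4, 8, 12 and 24, with not every measure taken at each.

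**Step 1. Reproduce the plan's figure.** With 20% attrition, 20 per arm remain. The formula is d = f × (z0.95 + z0.80) × √(1/n1 + 1/n2), with z0.95 + z0.80 = 1.645 + 0.842 ≈ 2.486 and √(1/20 + 1/20) = 0.316.
- Baseline-adjusted, f = √(1 − 0.50²) = 0.866: d = 0.681. Power at d = 0.7 is 0.819.
- Simple change score, f = √(2 × (1 − 0.50)) = 1: d = 0.786 with 20 per arm and 0.703 with 25 per arm.
- 0.7 × 27 = 18.9, about 19 points.

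The stated figure reproduces with attrition under baseline adjustment.

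**Step 2. Is power the problem?** Hardly. Starting from 20 against 20, losing 3 more from TXT-CBT lowers baseline-adjusted power at d = 0.7 from 0.82 to 0.79. Losing 5 more lowers it to 0.77. The question is bias.

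**Step 3. Size of a possible bias (assumption).** The article gives no exit counts. Suppose k of 25 TXT-CBT participants leave by these routes, nobody leaves usual care, and the leavers' outcomes would have been D SD worse than the stayers'. The full-arm mean is the stayers' mean minus (k/25) × D, so the completer mean is too favourable by (k/25) × D × 27 points. The last column is the one-sided type I error of a cross-sectional completer comparison at nominal 0.05, with standard error √(1/25 + 1/(25 − k)) in SD units.

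| k | Bias, D = 0.5 | Bias, D = 1 | Type I error, D = 0.5 to 1 |
|---|---|---|---|
| 1 | 0.54 | 1.08 | 0.058 to 0.066 |
| 2 | 1.08 | 2.16 | 0.066 to 0.086 |
| 3 | 1.62 | 3.24 | 0.075 to 0.109 |
| 5 | 2.70 | 5.40 | 0.095 to 0.164 |

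Against 19 points the range is 0.54/19 = 3% to 5.40/19 = 28%. The row k = 5 gives the whole 20% allowance for that arm (0.20 × 25 = 5) to these two routes.

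**Step 4. Can data collected before exit help?** That depends on the measure (Table 1).
- Pill counts, urine screens and Timeline Followback are taken at weeks 4 and 8 as well. A random effects model can use those values for someone who leaves before week 12.
- The Addiction Severity Index, the Behavioral Risk Assessment, viral load and the Drug-Taking Confidence Questionnaire are taken only at baseline, week 12 and follow-up. Someone who leaves before week 12 contributes a baseline value and nothing later on these.

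**The case against.** The other side has substance.

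- **STOP is conditional.** The sentence offers a way out to people who already wish to leave the study. It does not say that someone who only wants fewer texts is dropped, and a request to leave the study is close to withdrawal of consent. This stands as a limit on the claim. What remains is that the only keyword described for stopping is attached to leaving the study, with no lesser option beside it.
- **LIFELINE does not remove anyone automatically.** It leads to a case-by-case consultation, and no removal is reported. This stands.
- **Usual-care participants can leave too.** Participants gave informed consent and nothing bars withdrawal in that arm, where loss may also be related to outcome. Only the route is arm-specific. This stands, and it is why the net direction is open.
- **The planned model uses data observed before exit** and is valid if loss depends only on what was observed. Depression and anxiety scales, urine screens and pill counts are taken at weeks 4 and 8, and staff review the text logs. This stands for the frequently measured outcomes, but not for those with no value between baseline and week 12.
- **This is a condensed article on a pilot sized for feasibility**, and follow-up after discontinuation is commonly left to the full protocol. That would answer a complaint about silence. The point here is what the text does say: both routes bear on participation in the study.

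A reader might infer that these rules create outcome-related dropout in TXT-CBT and that the effect is therefore overstated. The documents do not support that: they report neither exits nor any link between exits and outcome.

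**Conclusion.** The point holds in a limited form. As worded, STOP and the LIFELINE review concern participation in the study, they operate after randomisation, and they run only through the TXT-CBT text system. They open an arm-specific route to possibly informative loss of week-12 and week-24 data.

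Direction and size are not known. The 0.5 to 5.4 points rest on three assumptions: 1 to 5 exits, outcomes 0.5 to 1 SD worse, and no offsetting loss in usual care. They describe a completer mean, not the planned random effects regression, for which they are likely an upper guide. The weakness is most relevant for the Addiction Severity Index, HIV risk behaviour, viral load and the aim 3 correlations. It is worth correcting because correction is cheap, not because harm has been shown.

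Separately, the allowance of three LIFELINE uses and the review at three or more do not sit together. Using the full allowance already triggers the review, and more than three should not occur under the stated total.

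**What to change.** - State that a STOP text ends messaging only, unless the participant also withdraws consent to follow-up.
- State that, whatever the clinician decides after a LIFELINE review about treatment or messaging, the participant is still invited to the remaining pill counts, the week-12 and week-24 assessments and the viral load release, with the usual payment, unless consent is withdrawn.
- Analyse these participants in the assigned arm.
- Report exits by arm, date and reason, keeping the end of messaging apart from the end of follow-up.
- The authors should reconcile the allowance of three LIFELINE uses with the review at three or more. No clinical rule is proposed here.

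The cost is a change to the STOP script and staff instruction, plus a few assessment payments. The means already exist: pill counts are done by phone, viral load can come from the provider by release, and payment is per assessment (Outcome Measures; ART Adherence). The Results section describes data collection as ongoing, so when the article was written it was still possible to invite anyone who had stopped and to report exits by arm.

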### Outcome Measures

See Table 1 for an overview of the outcome measures. Primary outcomes included ART adherence, substance use, and HIV risk behaviors. ART adherence was assessed by phone using an unannounced pill count (UPC) procedure. All other outcome measures were administered in face-to-face interviews, with some clinician-administered measures and the majority of the assessments conducted using a Web-based data entry system. Participants were compensated in gift cards as follows: $40 for the baseline assessment, $20 for each monthly face-to-face assessment, and $20 for each phone-based pill count procedure. Additionally, for bringing in photocopies of viral load and CD4 count assay reports from their primary HIV care provider, participants were compensated $20 at baseline (BL), treatment end, and follow-up.

### Primary Outcomes

#### Substance Use

Substance use was assessed using urine drug screens, the Addiction Severity Index, and the Timeline Followback (TLFB) method. Urine drug screens were collected at baseline and weeks 4, 8, 12, and 24 using temperature-controlled test cups. A US Food and Drug Administration–approved one-step, rapid dip drug test is used (CLIAwaived Inc). The urine drug screens tested for the presence of amphetamines, benzodiazepines, methadone, cocaine, methamphetamine, barbiturates, oxycotin, opiates, and marijuana.

The Addiction Severity Index [51], collected at baseline, treatment end, and follow-up, was used to assess psychiatric and substance use disorder severity and other domains of functioning. Composite scores (alcohol and drug, psychiatric, legal, family, and employment) will be contrasted between groups at baseline to evaluate the effectiveness of randomization. Drug use severity composite scores will be used as a covariate in the analysis of differential treatment effects on outcomes.

The TLFB, a calendar-assisted structured interview [52] with demonstrated validity in substance treatment samples [53], was used to assess drug use in the preceding 90-day period at baseline and follow-up and preceding 30-day drug use at weeks 4, 8, and 12. The TLFB was used to calculate self-report substance outcome variables including percent days abstinent as reported in Project MATCH [54]. Time to first relapse was also evaluated using the TLFB. As in prior work [55], relapse was defined as the first drug use following 7 consecutive days of abstinence after the initiation of treatment.

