#### Cognitive Behavioral Therapy for Substance Use Disorders

Both behavioral and cognitive-behavioral treatment approaches have therapeutic effects on a range of functional outcomes among adults with drug use disorders [16]. Although CBT has been evaluated empirically for the treatment of drug users, no studies to date have used mobile phone technology to deliver this intervention to drug-dependent populations.

CBT is among the most widely studied psychosocial interventions for substance users in well-controlled randomized trials. The therapeutic effects of CBT are robust and have been well established across various substance using populations, including those who are dependent on opioids [17-20], marijuana [21], alcohol [22], and stimulants [23]. Based upon social learning theory, a central assumption of CBT treatment is that substance dependence emerges from a process whereby the individual learns through experience about the reinforcement value of the substance [24]. Anticipated reinforcement is thought to drive continued and problematic behavioral patterns of substance use. CBT therefore focuses on the goal of facilitating abstinence from substance use by teaching new alternative, reinforcing behaviors.

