### Aims

This paper describes the methodology leading to the development and pilot testing of a CBT-based text messaging intervention (TXT-CBT) targeting ART adherence and drug use. Although there are features of CBT such as direct therapist feedback concerning therapy homework, for example, that cannot be replicated using a predominantly automated text messaging platform, the TXT-CBT program transports the essential features of CBT for relapse prevention to the technology-assisted platform, with recognition of these inherent limitations. Some of the limitations imposed by a technology-based approach are mitigated by the involvement of a clinician in the TXT-CBT intervention program.

The purpose of this study was to develop, with user feedback, a 12-week CBT-based text messaging treatment program targeting ART adherence and drug use and test its efficacy through a pilot randomized clinical trial. The specific aims of the study were to (1) test the impact of TXT-CBT over and above usual care for HIV on substance use and health care outcomes, (2) evaluate the differential effect of TXT-CBT versus usual HIV care on HIV risk behavior and ART adherence, and (3) examine potential mechanisms of action of TXT-CBT.

The following hypotheses addressed the goals of the study:

Among substance-dependent adults receiving HIV care, TXT-CBT would yield superior clinical outcomes relative to usual care in reducing substance use and health service utilization during and after treatment. In particular, while some health care utilization may increase among those who benefit from TXT-CBT (eg, use of routine HIV care services), we anticipate reductions in hospitalizations and emergency care services secondary to substance use.TXT-CBT would have superior effects on ART adherence and HIV risk behaviors relative to usual HIV care.TXT-CBT would have a direct effect on psychological variables that are recognized mechanisms of change in CBT treatment for addicted populations (negative affect, self-efficacy, social support). Specifically, we predicted that reductions in negative affect and cravings and increases in self-efficacy and social support would be positively associated with retention in TXT-CBT and inversely related to substance use during and after treatment.

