### Target/Study Population

Inclusion criteria were (1) age 18 years or older, (2) Diagnostic and Statistical Manual of Mental Disorders, 4th. Edition (DSM-IV) diagnosis of opioid or stimulant dependence, (3) HIV-infected and currently taking ART prescribed within the past 30 days, and (4) currently own a cell phone that can send and receive text messages. Exclusion criteria were (1) lack of proficiency in English; (2) currently homeless (unless residing in a recovery home for which contact information can be provided); (3) dependence on an illicit substance for which medical detoxification is imminently needed; or (4) presence of clinically significant psychiatric symptoms as assessed by the M.I.N.I. International Neuropsychiatric Interview such as psychosis, acute mania, or suicide risk that would require immediate treatment or make study compliance difficult.

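### Time to first relapse requires 7 abstinent days after randomisation, so continuing users cannot have the event and the comparison between arms can be distorted or reversed

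*Protocol article*

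**What the plan says.** Substance use is one of three primary domains in the Outcome Measures section: "Primary outcomes included ART adherence, substance use, and HIV risk behaviors". Under Primary Outcomes, Substance Use, the TLFB supplies "self-report substance outcome variables including percent days abstinent". The same paragraph adds: "Time to first relapse was also evaluated using the TLFB". Following prior work, it states that "relapse was defined as the first drug use following 7 consecutive days of abstinence after the initiation of treatment".

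Eligibility (Target/Study Population) requires a "diagnosis of opioid or stimulant dependence". No listed criterion asks for abstinence or completed detoxification at entry. The article gives no rule for a participant who never has 7 abstinent days. Statistical Analyses describes random effects regression and does not mention time to relapse.

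**The concern.** The background section states the aim of the treatment: "CBT therefore focuses on the goal of facilitating abstinence from substance use by teaching new alternative, reinforcing behaviors". The first hypothesis is that "TXT-CBT would yield superior clinical outcomes relative to usual care in reducing substance use and health service utilization during and after treatment". If TXT-CBT works, more of its participants should reach 7 consecutive abstinent days. Under the stated rule, reaching that run is also what makes a person able to relapse. Entry to the risk set is thus a response to treatment.

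Two ways of handling those who never reach 7 days fit the definition as written, and neither gives a sound comparison:

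- **Keep them as event-free.** A person who uses at least once in every 7 days gets the best possible result.
- **Leave them out.** The arms are then compared in subgroups formed after randomisation, and randomisation no longer protects the comparison.

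The pilot is meant to explore effect sizes before a larger, fully powered trial. A relapse result that is attenuated or has the wrong sign would misinform that step.

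**Working it through.** The plan attaches no figure to time to relapse, so there is none to reproduce. Its detectable effect of d=.7 concerns differential change in outcomes and does not bear on this point.

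**1. Algebra.** Let *a* be the share of an arm that ever reaches 7 consecutive abstinent days, and *r* the share of those who use again within the observation period.

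- Relapse under the stated rule, all randomised participants kept: *a × r*.
- Failure if the never-abstinent also count as failures: *1 − a × (1 − r)*.
- TXT-CBT looks worse under the stated rule whenever *a × r* is larger in TXT-CBT than in usual care.

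The article gives neither *a* nor *r*, so every value below is an assumption. Each pair is usual care v TXT-CBT.

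| *a* | *r* | Relapse as stated | Never-abstinent counted as failures |
|---|---|---|---|
| 30% v 60% | 80% v 60% | 24% v 36% | 94% v 76% |
| 30% v 60% | 80% v 40% | 24% v 24% | 94% v 64% |
| 50% v 70% | 70% v 60% | 35% v 42% | 85% v 72% |
| 60% v 80% | 80% v 50% | 48% v 40% | 88% v 60% |

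In all four rows TXT-CBT is better on both components. The stated rule shows it as worse in two rows, equal in one and better in one.

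**2. Independent daily use (simulation).** Each person has a fixed daily probability of use, drawn from Beta(2,2) in usual care (mean 50%) and Beta(1,3) in TXT-CBT (mean 25%), over 84 days.

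- Reaching 7 abstinent days: 41% v 80%.
- Relapse as stated: 41% v 76%. Over 168 days: 50% v about 85%.
- Relapse among attainers only: about 99% v 95%. The direction is now favourable, but the comparison sets 41% of one arm against 80% of the other (about 10 v 20 of 25), and a halving of drug use shrinks to 4 points.
- Relapsed or never abstinent: 99% v 96%.
- Percent days abstinent: 50% v 75%, by construction.

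**3. Episodic use (simulation).** 80% are using at the start. The daily chance of stopping is 5% in both arms, and the daily chance of returning to use is 3% v 1.5%, over 84 days.

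- Reaching 7 abstinent days: about 97% v 98%.
- Relapse as stated: about 78% v 57%, the right direction.
- Adding the never-abstinent: 78 + 3 = 81% v 57 + 2 = 59%.
- Percent days abstinent. The long-run share of using days is 0.03/0.08 = 0.375 v 0.015/0.065 = 0.231. Averaging the approach from 0.80 over 84 days gives 0.375 + 0.425 × (1 − 0.92^84)/(84 × 0.08) = 0.438 v 0.231 + 0.569 × (1 − 0.935^84)/(84 × 0.065) = 0.335. Days abstinent are therefore 56% v 67%.

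**4. Range.** Other independent-use settings over 84 days mostly reverse. Mean daily use of 0.6 v 0.4 gives relapse of 24–30% v 55–57%. One setting does not reverse: daily use of 0.30 v 0.15 with high variation between people gives 62% v 58%.

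**5. Are the data there for another definition?** The TLFB covers the "preceding 90-day period at baseline and follow-up and preceding 30-day drug use at weeks 4, 8, and 12". The gaps between weeks 0, 4, 8 and 12 are 28 days and the gap from week 12 to week 24 is 84 days. The windows therefore span about 168 days after baseline without a break.

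**The case against.** The article states an event definition, not a full time-to-event specification. The risk set and censoring rule may stand in a full protocol or analysis plan that is not shown. A reader might infer that the plan scores never-abstinent participants as non-relapsers; the article does not say so. What stands is narrower. Under the printed definition such a person has no event, and both ways of applying it unchanged are unsound. Counting these people as failures would be a change to the definition.

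A reader might also infer that an effective TXT-CBT would be expected to look harmful, with 41% v 76% as the forecast. The documents do not support that. They give no use rates, and the independent-day model leaves relapse among attainers at 99% v 95%, so it allows almost no relapse-prevention effect, although half of the non-reminder messages target relapse prevention. The episodic model does not reverse. Recovery-home residents are eligible and recruitment draws on treatment programmes, so some participants may enter already abstinent, which weakens the mechanism.

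Nor does the point undermine the trial's main comparisons. Time to relapse is an additional TLFB variable beside percent days abstinent, urine screens and the Addiction Severity Index. The between-group analyses are called exploratory, and sample size was set by feasibility.

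Finally, the clock starts at treatment initiation, and usual HIV care was already under way in both arms. This looks like an asymmetry, but the comparator is itself named treatment as usual and both arms share an assessment schedule, so a common start is a natural reading. It is a minor wording point.

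**Conclusion.** The point holds at moderate severity. It follows from the wording alone that a participant without 7 consecutive abstinent days cannot have the event, and that eligibility for the event depends on a response that TXT-CBT aims to produce. The measure can therefore misstate or reverse the treatment effect. Whether it does, and by how much, rests on assumed use patterns: 41% v 76% under independent daily use, about 78% v 57% under episodic use with return to use halved. In both of these scenarios percent days abstinent points the right way (50% v 75%; 56% v 67%).

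**What to change.** Before the analysis:

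- Use time from randomisation, in both arms, to the first 7 consecutive abstinent days as the between-arm TLFB time-to-event measure. This also settles the start of the clock.
- Report relapse only descriptively, among those who attain 7 days, with the number attaining in each arm.
- If relapse is kept as a between-arm comparison, count never-abstinent participants as failures at day 0. This is the second choice, because under independent daily use the proportion failing barely separates the arms (99% v 96%).
- Let percent days abstinent carry the between-arm TLFB comparison of drug use. This matters because time to first abstinence would show little if TXT-CBT acts mainly by preventing return to use, as in the episodic scenario.

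The cost is the redefinition of one derived variable from calendar data already being collected. The downside is that the relapse result becomes less comparable with the prior work that used this definition.
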